### 2.2. Family Recruitment and Eligibility

The Spanish families will be recruited by researchers from the Nutrition and Health Unit (Eurecat, Reus) and the Center for Research in Agri-Food Economics and Development (CREDA, Barcelona), and the Turkish and Moroccan families will be recruited by researchers from the Bursa Uludag University and the Unité de Nutrition et al.imentation CNESTEN, respectively. In addition, all countries will have the support of schools, high schools, family associations, and other collaborators such as primary care centers and community centers.

Families will be eligible to participate if they meet the following criteria: (a) families from any socioeconomic status with at least one child younger than 12 years and one adolescent older than or equal to 12 years (overall age range 3–17 years) and that live together; (b) informed consent has been signed by parents and the adolescent; and (c) families have a mobile phone, tablet, or computer with internet access. This inclusion criterion of composition of families and ages of children was selected to capture a range of developmental stages within families, as younger children and adolescents may respond differently to dietary interventions than adults. While this may introduce differences in family structure, it also promotes interaction across ages, potentially enhancing the adoption of healthy eating habits through sibling influence and parental support.

Exclusion criteria will be as follows: (a) having allergies or food intolerances to any of the following plant-based snack ingredients: fruit, vegetables, legumes, cereals, seeds, nuts, and yogurt (only for children under 12 years); (b) disliking any of the snack products (only for children under 12 years); (c) MD Adherence Score (MEDAS) or KIDMED score greater than or equal to 11 points, which is a food pattern already highly concordant with the MD [36]; (d) following a vegan diet (any of the family members); (e) following a prescribed long-term and strict diet for any reason, including diets for weight loss and diets for chronic metabolic or autoimmune disorders such as type 1 diabetes, celiac disease, inflammatory bowel disease, or rheumatoid arthritis (any of the family members); (f) participating in or having participated in a clinical trial or nutritional intervention study in the last 30 days prior to inclusion in this study; (g) no or limited access to the internet; and (h) being unable to follow the study guidelines.

All recruited families will be interviewed by expert nutritionists to assess whether they meet the conditions for inclusion. For this purpose, two principal researchers in each country will be responsible for explaining the background, purpose, process, risks, and benefits of this study and obtaining informed consent.

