To evaluate the overall effect of the intervention as well as the individual and combining effect of each intervention component, a full-factorial design will be used [34]. This design will allow us to evaluate the independent effect of the different intervention components versus the control group and, simultaneously, the summatory effect of combining different components on increasing the family adherence to the MD. This will therefore provide a stronger inference about the effect on the different implemented interventions [35].

The overall study duration will be 13 months for each participating family, including 3 main visits (V0, V1, and V2) (Figure 2). A prior preassessment visit will be performed at baseline, followed by the intervention study that will be deployed in the last 3 months (between month 10 and 13). According to this timeframe, this study will be arranged in two different phases (Figure 2).

*Phase 1* (*month 0 to month 9*): preassessment. The families will be recruited and included in this study; they will be randomly assigned to the different study groups; and consumption patterns and sociodemographic, socioeconomic, and environmental indicators will be evaluated through specific questionnaires. In addition, the different educational materials and activities, AI-based app, and healthy plant-based snacks will be developed prior to the start of the intervention study. This information will help us understand the context of each participant group and inform our analysis.

*Phase 2* (*month 10 to month 13*): the intervention study will be deployed at the family level. Families will receive the educational materials and activities, the AI-based app, and the plant-based snacks developed in Phase 1, depending on their assigned intervention group. In addition, anthropometrics, lifestyle, dietary, and socioeconomic and environmental indicators will be evaluated through specific questionnaires.

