#### 2.3.3. Healthy Plant-Based Snacks

The healthy and sustainable plant-based snacks will be developed and produced during Phase 1 of this study by three food companies located in Spain (DELAFRUIT S.L.U., Tarragona), Morocco (ECOMAB SARL, Casablanca), and Turkey (KOCAHAN SEKERLEME, Bursa) and will be consumed during the 3-month intervention by children aged 3 to 11 years.

The composition of the new food products will be based on local and traditional vegetables, fruits, legumes, seeds, and nuts as main ingredients, which are rich in health-promoting bioactive compounds. Processing and preservation strategies will be adapted to retain the nutritional value of the ingredients, and an eco-design methodology will be followed to produce the snacks [40]. In addition, the selection of the ingredients will be carried out beforehand in the three study countries through participatory focus groups involving parents and children. The locally produced plant-based ingredients will be presented to the families to determine their level of knowledge of them and the degree of incorporation in their diets (Table 2). The results of the focus group will allow the food manufacturers to reach a better understanding of the fruits, nuts, and vegetables the children usually consume in each country. Finally, after the preindustrial scale-up, four different snack prototypes to be used during the intervention in each country will be chosen according to the family’s preferences, and the portions and frequency of consumption will be defined to complement the children’s mid-morning and mid-afternoon snack, considering their nutritional and energy needs.

Since the snacks are produced with healthy and Mediterranean ingredients free of toxic agents and contaminants, no problems relating to children’s safety are expected during the intervention study. At the time of family selection, the children’s allergy history will be checked and the organoleptic characteristics of the snack products will be described to parents to verify the children’s acceptance.

The snack products will be produced in a single batch in each country. Once produced, the manufacturers of each country will send them to the corresponding enrolment center prior to the start of the intervention study. The products will be delivered in a lot to the families in the same country at the beginning of the intervention.

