### 2.4. Visits and Procedures

All families will attend the school facilities or at research centers where they are recruited on 3 different occasions (V0, V1, and V2). The visits will be divided between the two study phases previously described. Figure 4 shows the schedule of each visit, which will follow the same timeline for each enrollment center.

In Phase 1, families will be recruited and a preassessment visit will be carried out (V0). At this point, families will be assessed against the eligibility criteria and then informed about this study in a group session. The informed consent document will be signed by parents and adolescents. The researchers will then instruct them on the completion of online questionnaires at home through the Microsoft Forms web-based application to assess socioeconomic, sociodemographic, lifestyle, and environmental indicators. This information will be valuable in predicting selected behavior sub-domains that will be evaluated based on a theoretical model derived from the COM-B model for behavior change. A theoretical model based on information on physical activity, food habits, lifestyle, and social behavior will be created, aiming to achieve the best outcomes via surveys that are not too long [41]. In addition, families will complete a 7-day semi-weighted food record (7DWR) to assess dietary habits and consumption patterns at baseline. After V0, the selected families will be randomly allocated to the different intervention/control groups.

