In Phase 2, the selected families will attend V1 and V2 at the beginning and end of the 3-month intervention study, respectively. In V1, families will receive group training according to the different intervention groups: on the use of the S2H app, on snack consumption, and/or on the use of educational materials and activities. In addition, each family will be visited individually by expert nutritionists who will assess adherence to the MD through the MEDAS and KIDMED questionnaires for adults and children, respectively, and will take anthropometric measurements (body weight, height, BMI, waist circumference, blood pressure, and heart rate) for each family member. Nutritionists will also complete a medical history, including the use of medications and/or supplements. At the end of V1, time will be left for families to self-complete online questionnaires through the Microsoft Forms web-based application. The questionnaires will be adapted according to the age of the family members to assess socioeconomic, lifestyle, dietary, and environmental indicators. In addition, families will complete a 7DWR and report food expenses during the week after V1.

During the 3-month intervention, families will use the different educational components and products. They will be in continuous contact with the research team to ensure compliance and report any adverse events, particularly in children assigned to consume the snack products. In V2, each family will be visited individually, the same parameters as those in V1 will be measured by nutritionists, and data on socioeconomic, lifestyle, dietary, and environmental indicators will be self-reported by each family member by means of online questionnaires. A closing session of this study will be carried out by researchers once the intervention is completed to inform the families of the main results of the study.

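### Age eligibility is checked at V0, but the age-targeted components start about ten months later, so some randomised families will have no child or adolescent in the stated age range at V1

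*Protocol article*

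**What the plan says.** Inclusion criterion (a) in Section 2.2 asks for "at least one child younger than 12 years and one adolescent older than or equal to 12 years", living together, with an overall age range of 3 to 17 years. It gives no date at which age is counted.

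Section 2.4 places the check at the preassessment visit V0: "At this point, families will be assessed against the eligibility criteria and then informed about this study in a group session". Allocation follows: "After V0, the selected families will be randomly allocated to the different intervention/control groups".

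Section 2.1 states: "The overall study duration will be 13 months for each participating family". The intervention occupies only months 10 to 13, with V1 at its start and V2 at its end.

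Two of the three components are aimed at an age group. The snacks "will be consumed during the 3-month intervention by children aged 3 to 11 years" (Section 2.3.3). The educational programme is designed for adolescents (Sections 2.1 and 2.3.2), although its toolkit also goes to their families.

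For the primary outcome, Section 2.4 describes the "MEDAS and KIDMED questionnaires for adults and children, respectively". Section 2.5 assigns MEDAS to parents and KIDMED to children. The abstract contrasts adults with children and adolescents.

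The Discussion mentions the interval between V0 and V1 only as a risk of drop-out.

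**The concern.** The age condition ensures that every family has someone to receive each age-targeted component. It is verified about ten months before those components are handed out, and the snack section defines recipients by age during the intervention. A child aged 11 years 4 months at V0 satisfies the criterion and is 12 at V1. An adolescent aged 17 years 4 months at V0 is 18 at V1 and outside the 3 to 17 range.

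The factorial comparison of a component with its absence assumes that the component can be received in the groups allocated to it. Under intention to treat, families without a recipient stay in their group and pull the contrast towards zero. Under per protocol, which Section 2.10.1 limits to families that exactly followed the instructions, the article does not say how to classify them.

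A smaller issue concerns the primary score. Under the adults-and-children wording, a member who turns 18 between V1 and V2 could be read as moving from KIDMED (stated range 0 to 12) to MEDAS (0 to 14).

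**Working it through.** **The plan's own figures.** Section 2.7 gives 45 families per group (SD 1.19, difference 1 point, alpha 0.05, beta 0.20). A two-sided two-sample calculation with alpha divided by the 28 pairs of 8 groups gives 45. Then 45/(1 − 0.25) = 60 per group and 60 × 8 = 480. These figures are not in dispute. In a full factorial of three components, each component is present in 4 of 8 groups, so 4 × 60 = 240 families are allocated to snacks and 240 to education.

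**Assumptions.** The documents give no age distribution. I assume uniform ages at V0, one child and one adolescent per family, V0 at month 0, V1 at month 10 and V2 at month 13.

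- Child band, 3 to under 12 years: 9 × 12 = 108 months.
- Adolescent band, 12 to under 18 years: 6 × 12 = 72 months.

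The share crossing the upper boundary within t months is t divided by the band width.

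**Crossing before the components start (t = 10).**

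- Children turning 12: 10/108 = 9.3%; 240 × 0.0926 ≈ 22 snack-group families.
- Adolescents turning 18: 10/72 = 13.9%; 240 × 0.1389 ≈ 33 education-group families.

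**Sensitivity to the age assumption.**

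- Younger children all aged 8 to 11 (48 months): 10/48 = 20.8%, or 50 of 240 snack-group families.
- Adolescents all aged 12 to 15: the oldest is just under 16 years 10 months at V1, so none has turned 18.
- Fixed sibling gap, with the younger child's age uniform over the feasible range:

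| Gap (years) | Children 12 or older by V1 | Adolescents 18 or older by V1 |
|---|---|---|
| 2 | 42% | 0% |
| 3 | 28% | 0% |
| 4 | 21% | 0% |
| 5 | 17% | 0% |
| 6 | 14% | 14% |
| 7–8 | 0% | 14% |

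- V0 spread over Phase 1, so that the gap to V1 averages 5.5 months: 5.5/108 = 5.1% of children and 5.5/72 = 7.6% of adolescents.

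The two halves trade off. Close siblings mainly lose the under-12 child, and widely spaced siblings mainly lose the adolescent. A second child within the age band lowers every figure.

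**Dilution, worst case.** Suppose a snack-group family without a recipient gains nothing at all. A 1-point effect then becomes 1 − 0.093 = 0.91 points. Power ≈ Φ(δ/(SD·√(2/n)) − z), with SD·√(2/45) = 0.251, so δ/0.251 is 3.99 at 1 point and 3.62 at 0.91.

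- Unadjusted pairwise test (z = 1.96): 97.9% falls to 95.1%.
- Bonferroni over 28 pairs (z = 3.12): 80.6% falls to 68.9%.

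These are upper limits on the loss. In combined groups the other components still reach the family, and main-effect contrasts use four groups on each side.

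**Score at 18.** Section 2.4 schedules MEDAS and KIDMED at V1 and V2, a 3-month window: 3/72 = 4.2% of adolescents, about 20 of 480. Section 2.10.1 also lists V2 against V0. If a V0 score is used there, the window is 13 months and the share is 13/72 = 18.1%.

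**The case against.** The strongest reply is that an article condenses the protocol, that age group may simply be fixed at enrolment, and that a reference date for age is the sort of rule that the full document would hold. If age group is fixed at enrolment, Sections 2.2 and 2.3.3 do not conflict. That is a possible reading, and the full protocol may say so. But the article does more than stay silent. It states when eligibility is checked, when the components are delivered, and the recipients' age during the intervention. Followed as written, these allow a snack family with no recipient.

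Other parts of the reply stand and limit the point. A reader might infer any of four stronger claims, none of which the documents support:

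- **About 28% of families (134 of 480) are affected.** This is 1 − (1 − 0.120)(1 − 0.181), the chance of any crossing by V2 with independent sibling ages. It counts children turning 12 in non-snack groups and adolescents turning 18 in non-education groups, where no component is lost. It also counts children still under 12 at V1, although the snacks are delivered in one lot at the start.
- **Change scores become impossible to compute.** A child turning 12 stays on KIDMED. Under Section 2.5 a sibling who turns 18 is not a parent, so KIDMED could continue. The wording is loose, but a switch is not prescribed.
- **Education families receive nothing.** The toolkit goes to adolescents and their families, activities are done at home with family, and no text stops delivery at an 18th birthday.
- **Withdrawals will differ by group.** Criterion (1) in Section 2.8 covers circumstances that prevent study procedures, including product intake. It does not mention age, so treating ageing out as a trigger is conjecture.

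Allocation is random, so crossings should be balanced across groups in expectation.

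**Conclusion.** The point holds in a limited form. The interval between the age check and the start of the age-targeted components is explicit, and the article neither re-checks age at V1 nor says how a member who has crossed a boundary is treated.

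Under uniform ages with one child and one adolescent per family, about 9% of snack-group families (22 of 240) would have no child aged 3 to 11 at V1, and about 14% of education-group families (33 of 240) would have no adolescent under 18. The first share rises to about 21% if the younger children are 8 to 11, and the second is near zero if the adolescents are 12 to 15. These shares rest on assumed ages, whereas the timing mismatch does not.

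The consequence is modest dilution of the component contrasts and uncertain per-protocol classification. It is not confounding or imbalance between groups. Which score applies to a member who turns 18 between V1 and V2 is a minor ambiguity, at about 4% of adolescents. The change is worth making because it is cheap and must precede recruitment to help.

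**What to change.** Reconcile Sections 2.2, 2.3.3 and 2.4:

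1. In inclusion criterion (a), count age at the planned V1 date, computed from date of birth at recruitment.
2. State that each member keeps the same adherence questionnaire (KIDMED or MEDAS) and the same analysis category from V1 to V2, and use the same adult, parent and child terms in Sections 2.4 and 2.5.
3. Have the sponsor specify how components are delivered to members who cross an age boundary and how their families are classified per protocol. This review proposes no delivery rule.

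The cost is a sentence or two and a date calculation at recruitment. The age window moves rather than narrows, so the recruitment pool should stay about the same size. A few members will be slightly over 12 or 18 at V2 and analysed in their V1 category. The lower limit moves too: a child who is 3 at V1 could be as young as 2 years 2 months at V0, so the V0 questionnaires should be checked for that age. If recruitment has already begun under the V0 rule, items 2 and 3 can still be fixed before unblinded analysis.

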### 2.3. Interventions

The interventions will involve a combination of digital-based tools and hands-on educational materials and activities, with healthy plant-based snacks developed during Phase 1 of this study. At the beginning of Phase 2 (month 10), there will be prior training for all families, where they will be informed about the specific intervention to which they will be randomly assigned.

The intervention materials and products will be adapted to reflect the cultural preferences and dietary habits of each country. This approach ensures that the interventions are relevant and engaging for families in each country. However, we will maintain some common elements across all interventions to facilitate meaningful comparisons in the study’s outcomes.

#### 2.3.1. Digital Interactive Tools

The digital interactive tools will be implemented in the form of an integrated web application, the “S2H app”, which will be used by parents to empower them in their daily family dietary choices. The S2H app will be based on the integration of two separate dietary apps and an educational dietary game that will be designed, developed, technically validated, and extensively tested with real users during Phase 1 of the study: AI-based app for parents, app for children’s Med-based dietary plan, and Digitami Game (Table 1). The two constituent dietary apps are, in turn, based on pre-existing technologies that have been validated in previous research projects with real users: the EU-funded PROTEIN project https://cordis.europa.eu/project/id/817732 (accessed on 9 September 2024) and the NUBI Parma app https://www.ailab.unipr.it/projects/ (accessed on 9 September 2024). Otherwise, the educational game will be developed entirely within the SWITCHtoHEALTHY project.

The S2H app engine is fed with (a) expert-approved dietary rules; (b) user profile data for all family members; (c) school menus (from the school catering system) or, alternatively, lunch box contents and school café proposals; and (d) a list of representative meals of the local Mediterranean cuisine, i.e., breakfasts, lunches, and dinners, along with caloric and macronutrient information (the latter for the parents only). The seasonality of each food and ingredient and the culinary traditions of the food area in which the app is used are also considered. All the contents in the S2H app will be available in 4 languages (English, Spanish, Turkish, and Arabic).

The users will be able to provide basic profile information for each family member, including their year of birth, sex, physical characteristics (weight, height, and BMI), physical activity levels, dietary preferences, and history of food allergies, and will then receive weekly meal plans for them, adhering to a healthy and sustainable MD. Conversely, more general information will be requested for child users regarding age group, allergy to milk proteins, consumption of the project snacks, and school name (for school menu) or lunch box and school café alternatives.

#### 2.3.2. Hands-On Educational Materials and Activities

The hands-on educational materials will be developed through a learning-through-playing approach to increase adolescents’ knowledge and motivation on healthy and sustainable food habits according to sustainable MD patterns. An MD toolkit will be provided to adolescents and their families to educate them on the MD and associated health benefits to encourage the consumption of more healthy foods. The materials of the MD toolkit will be designed during Phase 1 of this study, including the following: (a) specific games and activities for adolescents, with proposed activities played at home with parents, brothers and sisters, and friends; (b) a range of resources, including educational fact sheets combining more theoretical notions about the MD model and optimal diet management (e.g., the “healthy eating plate”, consumption frequencies, and food portions for different ages), infographics with take-home messages, recipes, and a short video. The educational materials will be available in different languages through the SWITCHtoHEALTHY website https://switchtohealthy.eu/ (accessed on 9 September 2024).

The educational activities will be part of an educational program specially designed to improve adherence to the MD of adolescents. The program will be conducted outside of school hours during the 3-month intervention and will be previously designed during Phase 1 of this study under the umbrella of three selected topics: (1) Mediterranean Diet and Lifestyle: discovering cultures, foods, and tastes; (2) Mediterranean Diet: from a healthy diet to a sustainable dietary pattern; and (3) Food Lab: kitchens from research or cooking centers as experimental hands-on zones for the application of healthy and sustainable dietary patterns. At least two cocreation sessions will be organized in each study country, with adolescents assigned to the educational activity groups as cocreators. The World Cafe Methodology [37,38,39] will be applied, encouraging participants to talk to each other and discuss the three selected topics in small groups in a cozy café-style space hosted by researchers as moderators (Ms) and high-school teachers as facilitators (Fs). Each session will take around one-and-a-half hours and will be joined by about 12 adolescents and at least 2 teachers and 2 researchers who will be neutral and encourage participation. The adolescents will be divided into three tables (4 to 5 adolescents per table) and, at each table, one of the three selected topics will be discussed so that the adolescents will rotate around every 20 min to participate in the discussion of all the topics (Figure 3). The researchers will record all the conversations that take place on a smartphone and will also take written notes. Once all the discussion rounds have finished and after a coffee break, the entire group will meet again in plenary. The resulting activities from each table will be summarized by researchers who will bring down the number of generated ideas to a handleable minimum, focusing on those factors generally considered to be the most important. Finally, the participants will vote on the results to prioritize actions to be implemented as educational activities in the frame of the educational program. After the cocreation session, all the data will be gathered and analyzed by the researchers in each country. The codesigned activities will then be reprioritized by all participants via an online survey. Lastly, the researchers will select and develop the 12 most voted educational activities, with 4 per topic, to be implemented within the framework of the intervention study.

During Phase 2 (month 10 to month 13), the codesigned activities will be carried out by adolescents at home (or in other nearby places, like markets) together with family and at research facilities together with the research staff. Four activities will be carried out on each selected topic in each month of intervention. Adolescents will be provided with a practical support handbook (or e-book) collecting all the activities and needed materials, which will be available and downloadable in different languages from the study website. Each activity will be described in the form of a didactic programing unit structured with the following sections: title, purpose, learning outcomes, preparation time and duration, methodology, materials required, and other resources. Due to the nature of this study, to avoid confounders in different intervention groups, these activities cannot be performed at school during the intervention. Nevertheless, the activity practical support handbook will be available for schoolteachers at the end of the intervention.

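### The toolkit games may be played with unrestricted friends, leaving open a peer route into the non-education groups that the purpose of the school ban should cover

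*Protocol article*

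**What the plan says.** All places are in the protocol article.

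- **Toolkit games (section 2.3.2, first paragraph).** The toolkit contains games and activities for adolescents, with "proposed activities played at home with parents, brothers and sisters, and friends". Friends are not limited to people outside the trial or to the education groups.
- **Codesigned activities (section 2.3.2, last paragraph).** The 12 activities of the educational programme are done at home or nearby "together with family and at research facilities together with the research staff". Friends are not mentioned here.
- **Safeguard (same paragraph).** The reason for keeping the programme out of school is given: "to avoid confounders in different intervention groups, these activities cannot be performed at school during the intervention". In line with this, "the activity practical support handbook will be available for schoolteachers at the end of the intervention".
- **Recruitment (section 2.2).** Besides the research teams, "all countries will have the support of schools, high schools, family associations" and other collaborators such as primary care and community centers.
- **Visits (section 2.4).** "All families will attend the school facilities or at research centers where they are recruited".
- **Allocation (section 2.6).** Families, not schools, are randomised in equal numbers to eight groups. In the full factorial of three components, four of the eight groups have no education component.
- **Limitations (section 3).** Exposure of one group to another group's component is not listed.

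**The concern.** The sponsor has already judged that spread of the education component between groups through school contacts is worth preventing, and has closed the classroom route. The toolkit text, however, actively proposes play with friends. An adolescent's friends are often schoolmates, schools are one of the recruitment channels, and every family in the trial includes an adolescent. A friend who belongs to another trial family, and who has no education component, is therefore a foreseeable co-player. Playing the game gives that friend part of the component, wherever it is played.

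What is at stake is the estimate the factorial design exists to provide: the independent effect of each component and the effect of combining them (section 2.1). Exposure of non-education adolescents raises the comparator and pulls the education effect towards zero, while the app and snack components have no such proposal to involve friends. Section 2.10.1 plans intention-to-treat and per-protocol analyses. Both are defined by a family's own allocation and adherence, so neither addresses exposure that comes from another family.

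**Working it through.** **1. Chance that an enrolled friend is a comparator.** Section 2.1 gives 160 families per country, 20 per group. Four groups without education make 4 × 20 = 80 families. For an education family, 80 of the other 159 families in its country are comparators: 80/159 = 50%. This is conditional on the friend being in the trial. The documents do not give the chance of that.

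**2. The plan's own sample size.** Section 2.7 gives SD 1.19, a difference of 1 point, alpha 0.05, beta 0.20, 45 families per group, and 60 after 25% dropout. It names analysis of variance but not the exact formula. A two-sample normal formula with Bonferroni correction over all 8 × 7/2 = 28 pairs, two-sided, reproduces the figure:

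n = 2 × SD² × (z for 0.05/28 + z for power)² / difference² = 2 × 1.19² × (3.124 + 0.842)² / 1² = 44.6, so 45 per group; 45/0.75 = 60.

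I take alpha 0.05/28 as the basis for pairwise power. It is a reconstruction and is not stated in the text. Without correction the same formula gives 23 per group.

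**3. Effect of exposure on the contrasts.** Let c be the share of families in each non-education group who receive the full education effect (assumed, and assumed equal in the four groups). For any combination of app and snack, the mean without education becomes (1 − c) × mean without + c × mean with. The education contrast is then

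mean with − [(1 − c) × mean without + c × mean with] = (1 − c) × (mean with − mean without).

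Interactions with education are differences between such contrasts, so they carry the same factor 1 − c.

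**4. Power for the education main effect.** Evaluable families: 4 × 45 = 180 per side. Standard error = 1.19 × √(2/180) = 0.1254. At two-sided alpha 0.05, power = Φ((1 − c)/0.1254 − 1.960). At c = 40%: Φ(4.783 − 1.960) = Φ(2.823) = 0.998. Smaller c gives higher power.

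**5. Power for a pairwise contrast of two groups that differ only in education.** Standard error = 1.19 × √(2/45) = 0.2509. Power = Φ((1 − c)/0.2509 − 3.124).

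| c (assumed) | Diluted difference | Power, 45 per group, alpha 0.05/28 | Evaluable families per group for 80% power |
|---|---|---|---|
| 0 | 1.0 | 0.81 | 45 |
| 10% | 0.9 | 0.68 | 55 |
| 20% | 0.8 | 0.53 | 70 |

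The last column shows only the scale of the loss. It is not a proposal to enlarge the trial.

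**The case against.** **The ban is not contradicted.** A reader might infer that section 2.3.2 breaks its own rule. It does not. The friends wording belongs to the toolkit games, whereas the school ban covers the codesigned activities, which are placed with family and research staff. This stands: there is a gap relative to the ban's purpose, and no breach of its wording.

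**Teachers.** A reader might also see a leak through the high-school teachers who facilitate the cocreation sessions. The text does not support much here. The creators are adolescents, "with adolescents assigned to the educational activity groups as cocreators"; the teachers are described as neutral; researchers select and develop the final activities; and teachers receive the handbook only after the intervention. I make no point of this route.

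**The exposure chain is uncertain.** It needs families who share a school or circle, adolescents who are friends, opposite education allocation, and enough play to change diet. Schools are only one recruitment channel. Treating a friend's game as the full component is an upper bound, since the game is only part of it. The 1-point difference in section 2.7 is on MEDAS, the parents' score, which an adolescent's game with a friend may barely move. This also stands, and it is why no value of c is claimed.

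**A general loss of power.** It is tempting to start from 80% power at a two-sided 0.05 and dilute from there. That matches nothing in the plan: at 45 per group, unadjusted power for 1 point is already 0.98. The education main effect keeps ample power even at c = 40%; what it suffers is bias.

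**Article detail.** Sharing instructions to families, and access to materials on the website, may be settled in the full protocol or handbook. Silence on those is no finding. The friends proposal is different, because the article states it positively.

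**Conclusion.** The point holds in limited form. The plan proposes play with unrestricted friends in a trial that randomises individual families, recruits partly through schools, and states that it wants to avoid spread between groups. The expected direction is attenuation of the education effect and its interactions by the factor 1 − c. The size cannot be determined from the documents and may be small.

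The main effect of education is at risk of bias, hardly of lost power. Pairwise contrasts that isolate education would lose power noticeably at c of 10% to 20%. These figures rest on four assumptions: full transfer of the effect to exposed families, equal c in the four non-education groups, the MEDAS figures of section 2.7, and, for the pairwise contrasts, the reconstructed alpha of 0.05/28. The case for acting rests on the very low cost of closing the route, not on any shown frequency of exposure.

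**What to change.** Two wording changes in section 2.3.2, carried into the adolescents' handbook:

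- In the toolkit paragraph, replace the open reference to friends with: *and friends who are not members of a participating family outside the education groups*.
- Beside the school ban, add: *Toolkit games and activities are not to be shared with members of participating families in non-education groups until the last V2.*

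Worded this way, education-group adolescents can still do activities together, including at the research facilities. A ban on contact with all other participating families would stop that for no gain.

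The cost is slightly fewer possible co-players and a sentence or two of instruction at the V1 training. Sample size, visits and analysis do not change, and no rule on the choice of facilitating teachers is needed.
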